#### Intervention description {11a}

##### Automated mechanical peripheral stimulation

AMPS therapy will be applied through a therapeutic device (Gondola, Ecker Technologies, Lugano, Switzerland), which will be fitted to each patient’s feet. The device consists of a foot stand for each foot with two electric motors that activate two 2-mm-diameter metal bars. The mechanical pressure stimulus occurs when the motors are activated. Before application, the device is adjusted so that the stimulus is applied to two specific areas for each foot, at the base of the first metatarsal joint and at the head of the hallux of the right and left feet. The intensity of the pressure is adjusted to reach the participant’s pain threshold (which normally occurs around 0. 3–0. 9 N mm^2^), defined as the moment when the participant reports that they began to feel pain (the moment of transition between the strong pressure and the painful pressure and the first time the visual analog scale (VAS) is greater than 0) or at the moment when the monosynaptic reflex appears in the anterior tibial muscle. After these preparatory procedures, treatment begins. The therapy will be carried out in 4 cycles. A cycle is completed when the four target areas are stimulated, which requires 24 s (6 s per area) so the complete therapy lasts 96 s [26].

The SHAM intervention will replicate the same procedure described for active AMPS. However, a rubber adapter will be positioned at the tip of the metal bars to increase the contact surface area and the pressure will be set to the sensorial threshold (i.e. when the patient report that they feel a touch at the point). AMPS sessions will be performed 24 h before all the exercise sessions [27].

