### Assignment of interventions: allocation

#### Sequence generation {16a}

A researcher not involved in this study will be in charge to generate the sequence number using a computerized algorithm (https://www.graphpad.com/quickcalcs/randomize2/). Participants will be randomly assigned, in a 1:1 ratio, to one of the two groups studied (1) exercise (coded as “A”) or (2) AMPS + exercise (coded as “B”).

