#### Implementation {16c}

Sequence number is generated by a researcher blinded to the study protocol. Opaque envelopes in numerical order will is then prepared and kept in a safe place until baseline assessments are concluded. Participants are recruited in the community, where the study takes place, by all researchers involved. Participants meeting the inclusion criteria proceed to the baseline assessments. Then, prior the beginning of the intervention the envelope labeled with the same number as assigned to the participants when they were included in the study will be unsealed and informed to the leading research. Figure 2 shows the study design flowchart describing all the steps of the study (Fig. 2).

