### Assignment of interventions: blinding

#### Who will be blinded {17a}

This will be a double-blinded study. Participants will be assigned to exercise plus AMPS or Exercise plus SHAM group. Thus, participants will be not aware if they are assigned to active AMPS or sham. Also, the researchers responsible for outcome assessments, data entry, and statistical analysis will be blinded to the group assignments. The leading research who will be in charge of the AMPS therapy will not be blinded, since it is not possible.

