#### Composition of the data monitoring committee, its role and reporting structure {21a}

The protocol excludes vulnerable people and people with diseases that may hinder the application of the protocol. So, it can be considered of low risk and of short duration, thus not requiring an additional committee [40].

The leading researchers ([name] and [name]) will meet every 2 weeks with all researchers involved in this study to monitor the data, discuss the research progress and any adverse event that arises during the procedures. Researchers are instructed to report any issue to the leading investigators immediately.

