#### Adverse event reporting and harms {22}

In the end of each intervention session, participants will be asked to report any complaints and symptoms produced by the proposed activity. Outcome assessor and the lead researcher will be in charge to collect and record this information throughout the study. Adverse events, undesirable effects, and incidents will be classified by specialists as treatment-related or non-treatment-related within 24 h of occurrence [41]. Common undesirable effects may include fatigue, dyspnea, and muscle soreness not lasting more than 24–48 h as a result of the exercise and AMPS intervention. In case these symptoms persist, or other related-treatment event occur, the participants will be asked to discontinue from this study and this will be immediately informed to the ethics committee who will decide whether the protocol should be suspended. All complications and dropouts will be reported in the final manuscript.

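### The harms section makes the outcome assessor collect complaints after each session, although the blinding section says assessors are blinded, and those complaints may expose the arm

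*Protocol article*

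**What the plan says.** The protocol article describes the trial as double-blind. Under Who will be blinded {17a} it commits that "the researchers responsible for outcome assessments, data entry, and statistical analysis will be blinded to the group assignments". The same section makes one exception: "The leading research who will be in charge of the AMPS therapy will not be blinded, since it is not possible". Implementation {16c} agrees with this, since the envelope "will be unsealed and informed to the leading research".

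Under Adverse event reporting and harms {22}, the timing of complaint collection is: "In the end of each intervention session, participants will be asked to report any complaints and symptoms produced by the proposed activity". The people responsible are named next: "Outcome assessor and the lead researcher will be in charge to collect and record this information throughout the study".

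The two stimuli are described under Automated mechanical peripheral stimulation. For active AMPS, "The intensity of the pressure is adjusted to reach the participant’s pain threshold". For sham, a rubber adapter widens the contact area and the pressure is set where the participant first feels touch.

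Two other places bear on the same topic. The section on the data monitoring committee {21a} says that the leading researchers "will meet every 2 weeks with all researchers involved in this study to monitor the data", and that adverse events are discussed there. Sequence generation {16a} prints the group letters, for example "AMPS + exercise (coded as" the letter B.

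**The concern.** The plan gives one role two duties that do not fit together. The outcome assessor is to stay unaware of the arm, and is also to hear and record, session after session, what participants felt, alongside the person who knows the arm. The sessions differ between arms in exactly the sensation that participants would be describing: painful pressure or light touch.

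An assessor who suspects the arm can influence results through encouragement in an effort-limited test, or through scoring and conduct of balance and gait tests. The protocol also states in advance that greater improvement is expected with active AMPS. What is at stake is the protection against detection bias that blinded assessment is meant to provide, and whether the double-blind label can be reported without qualification.

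**Working it through.** No figure in the plan depends on this point, so the check sets the sections side by side.

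**1. Roles.** {17a} has assessors blinded and the AMPS operator unblinded. {22} gives the outcome assessor and the lead researcher joint charge of complaint records. Assuming that the lead researcher in {22} is the leading researcher in {17a} and {16c}, a blinded and an unblinded person share one task throughout the study.

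**2. Does the information differ by arm?** Yes, by design. Active stimulation uses 2-mm metal bars at the pain threshold (or at the point where a reflex appears). Sham uses a rubber adapter at the touch threshold. Pain at the sole would suggest active treatment. Repeated absence of any foot sensation worth mentioning would suggest sham.

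**3. How often?** The plan has 2 sessions a week for 12 weeks: 2 × 12 = 24 AMPS or sham sessions per participant. AMPS is given 24 h before each exercise session, so there are also 24 exercise sessions. If both kinds count as intervention sessions, complaints are taken up to 24 + 24 = 48 times, of which 24 directly follow stimulation. If complaints are taken only after exercise, they come about a day after the stimulus and are less telling. The text does not say which applies.

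**4. Which outcomes could be affected?**

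| Outcome | Status | How obtained | Exposure to an assessor who suspects the arm |
|---|---|---|---|
| VO2peak | Primary | Incremental ramp test, breath-by-breath gas analysis | Yes, through participant effort rather than the reading |
| PDQ-39 | Primary | Questionnaire | Less |
| HRV indices | Primary | Heart rate monitor at rest | Less |
| Tinetti | Secondary | Balance and gait scale | Yes, through scoring |
| TUG | Secondary | Test plus an instrumented version | Yes; the instrumented version limits it |
| 10-m walk | Secondary | Best of three, registered by two evaluators | Yes; two evaluators limit timing error |
| 24-h blood pressure | Secondary | Device | Less |
| Sleep | Secondary | Actigraph | Less |

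VO2 at the anaerobic threshold comes from the same exercise test. The article does not describe how the threshold is read, so it is not classified here.

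One of the three primary outcomes is therefore exposed, and two of the five secondary groups (dynamic balance and gait velocity).

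**5. Would the plan detect a problem?** The guess-and-confidence question at 6 weeks and at the end is put to participants. It gives no information on whether assessors could tell the arm.

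**The case against.** The strongest reply is that nothing in the article says that an assessor is told the allocation or is present during stimulation. The effects that {22} lists as common are fatigue, dyspnea and muscle soreness, and both arms receive the exercise that can cause these. Foot pain is not listed. Stimulation lasts 96 s and stops at the first transition to pain, so recorded foot complaints may be rare. All of this stands, and it is why the point is one of exposure: a reader might infer that blinding is broken, but the text does not show that.

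Three further inferences are tempting and are not supported.

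- A reader might infer that the two-weekly meetings unblind everyone, because the AMPS operator discusses data and adverse events with all researchers. No section says that allocation or arm-specific detail is shared there, and the commitment in {17a} can be kept in such a meeting.
- A reader might infer that the printed A/B key unblinds the analyst. The letters are described only for the sequence and the envelopes. Data management {19} says only that the database is anonymised and coded. Labels for the analysis file may properly be set in a document that is not shown.
- A reader might infer a bias toward AMPS of some known importance. The stated hypothesis makes that direction plausible, but it is not demonstrated. The article also does not say that the walk is hand-timed, and it has two evaluators register the time.

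The reply does not remove the conflict between {17a} and {22}. Both are affirmative statements about the same role, so neither can be put down to detail left out of an article.

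**Conclusion.** The concern holds in a limited form. Followed as written, {22} puts the outcome assessor repeatedly in contact with information that may reveal the arm, which undermines the assessor blinding claimed in {17a}. The exposure is up to 24 stimulation sessions per participant. It matters for VO2peak among the primary outcomes and for Tinetti, TUG and the 10-m walk among the secondary ones. The size of any bias cannot be derived from the document, and its direction is not shown.

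The conclusion rests on two assumptions: that the outcome assessor in {22} is the person, or one of the people, covered by {17a}, and that complaints after stimulation are among those collected. The wording supports both. The conflict between the two sections is certain. How much arm information would actually pass is not known. The meetings and the group letters are secondary precautions and are not established failures of blinding.

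**What to change.** Reconcile {17a} and {22}. Take the outcome assessor out of complaint collection. Give the task to the session supervisors, of whom at least two already attend every session, on condition that they assess no outcomes. Keep the complaint records apart from the assessment files until assessments are complete. It is better not to rely on the AMPS operator alone for this task, because an unblinded recorder of subjective complaints can bias the harms comparison.

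Two secondary safeguards are worth adding:

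- When blinded staff attend the two-weekly meetings, discuss adverse events without arm or AMPS detail.
- If the analysis file would otherwise carry the published A and B letters, use neutral labels instead.

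The change moves an existing task and may relabel one variable. Its real cost is that supervisors and assessors must be different people among the existing staff, at both sites. The article does not say whether that is already so. The change can go to the ethics committee by the amendment route in {25}, and it leaves the interventions, their schedule and the harms questions as they are.

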#### Frequency and plans for auditing trial conduct {23}

The trial conduct will be continuously monitored by the principal investigators ([name] and [name]) and it will be discussed in the periodic meetings occurring every 2 weeks with all researchers involved. This trial was approved by the scientific ethics committee of the Catholic University of Maule and since the interventions (i.e. assessments and treatment) are considered of low risk, the supervision by an independent data monitoring committee was not required or considered for this study. However, as aforementioned, the researchers are committed to report any adverse events occurring during the study to the Ethics committee.

#### Plans for communicating important protocol amendments to relevant parties (e.g., trial participants, ethical committees) {25}

In case of any change in the current protocol, the principal investigator will be responsible for reporting and submitting the new version to the ethics committee for approval. After approval, the clinical record will be updated and all modifications will be reported.

#### Dissemination plans {31a}

Each participant will receive a full report with the results of their assessments. By the end of the study, the lead researcher will contact all the participants to provide the final results of the trial.

## Discussion

Several non-pharmacological treatment modalities have been proposed in the treatment of PD, focusing primarily on the treatment of motor and musculoskeletal disorders [42]. In this context, regular exercise and motor training have been shown to be effective in improving people’s quality of life, balance, physical functioning, and activities of daily living, and are therefore strongly recommended for patients with PD [43].

An analysis of the potential benefits of exercise in people with PD concluded that exercise could improve physical functioning, health-related quality of life, leg strength, balance, posture, walking and fitness [44]. Therefore, the authors’ statement that exercise improves functional motor performance in PD patients appears robust; however, the question remains as to which exercise protocol is most appropriate for individual patients [16]. In summary, the evidence base for treating a variety of non-motor symptoms in PD has grown substantially in recent years. However, treatment options in general remain limited given the high prevalence and adverse impact of these disorders, so the development and testing of new treatments for non-motor symptoms in PD remains a priority [45].

In this sense, some authors have proposed the use of AMPS as complementary therapy. This therapy has shown to provide promising effects such as better performance in the gait pattern [37] and decrease the treating freezing of gait [46]. Also, a single session of AMPS treatment is able to modify the resting state in regions of the brain and cerebellum [47], changes the shuffling steps pattern (that is typical of PD subjects), increases the shuffling steps pattern of hip, knee and ankle joints during the gait cycle [23]. In addition, AMPS treatment induces an increased activation of brain areas involved in the visual-space and in the sensory-motor integration [48], which could explain the positive effects on bradykinesia and several gait parameters [49].

Another point that must be mentioned is that patients with PD present disautonomia [50] and high prevalence of cardiovascular diseases [51]. It is well established that exercise is effective in improving cardiac autonomic control, usually quantified by heart rate variability indices, which is considered a prognosis marker for cardiovascular mortality [52, 53]. In the same line, some studies have shown that AMPS may improve the cardiovascular autonomic control [20, 21]. However, despite the positive effects of exercise and AMPS for patients with PD, no studies have addressed its long-term effects combined with an exercise program, since it is a relatively new intervention. Therefore, this study may help to elucidate the potential beneficial effects of adding AMPS to a rehabilitation program. If AMPS provides positive results, it may represent a new therapy strategy for patients with PD complementary to the physical exercise.

Our hypothesis is that the exercise program combined with AMPS therapy would be more effective in improving cardiac autonomic control and aerobic functional capacity in PD patients than exercise alone. This can be explained by two aspects. First, the combination of interventions can change brain functioning strongly than only exercise. While AMPS presents potential to change sensory-motor integration [54], exercise promotes consistent benefits on brain functioning and body system, but without consistent effects on sensory-motor integration. Second, the application of AMPS before the exercise can improve the performance of patients with PD during exercise. The positive effects of AMPS on walking and balance [55] can increase the exercise intensity and quality of movements during the exercise session. Increasing exercise intensity is an important component to improve the benefits of exercise in PD [56]. Thus, in case our hypothesis is confirmed, patients with PD submitted to physical exercise program combined to AMPS could have a greater improvement in their functionality, quality of life and cardiac autonomic control.

### Trial status

Version 4. November 01, 2021.

Date recruitment begins: July 30, 2021.

Approximate date when recruitment will be completed: October 31, 2022.

## Abbreviations

PD: Parkinson’s disease
AMPS: Automated mechanical peripheral stimulation
GEX: Exercise group
GAMPS: AMPS group
HRV: Heart rate variability
LF: Low frequencies
HF: High frequencies
SBP: Systolic blood pressure
HR: Heart rate
HO: Orthostatic hypotension
Vo2: Maximum oxygen uptake
VAS: Visual analog scale
BDNF: Brain-derived neurotrophic dactor
PDQ-39: The Parkinson’s Disease Questionnaire
TUG: Timed up and go
CESFAM: Family Health Center
CPET: Cardiopulmonary exercise testing
VCO2: Carbon dioxide output
VE: Ventilation
RER: Respiratory exchange ratio
EGG: Electrocardiogram
